## Abstract

**Background:**

In the intensive care unit (ICU), many patients are unable to communicate their pain through self-reporting or behaviors due to their critical care condition, mechanical ventilation, and medication (eg, heavily sedated or chemically paralyzed). Therefore, alternative pain assessment methods are urgently needed for this vulnerable patient population. The Nociception Level (NOL) index is a multiparameter technology initially developed for the monitoring of nociception and related pain in anesthetized patients, and its use in the ICU is new.

**Objective:**

This study aims to validate the NOL for the assessment of nociception and related pain in critically ill adults in the ICU. Specific objectives are to examine the ability of the NOL to: (1) detect pain using standard criteria (ie, self-report and behavioral measures), (2) discriminate between nociceptive and nonnociceptive procedures, and (3) generate consistent values when patients are at rest.

**Methods:**

The NOL will be monitored in three ICU patient groups: (1) Group A, participants able to self-report their pain (the reference standard criterion using the 0-10 Faces Pain Thermometer) and express behaviors; (2) Group B, participants unable to self-report but able to express behaviors (the alternative standard criterion using the Critical-Care Pain Observation Tool); and (3) Group C, participants unable to self-report and express behaviors. The NOL will be tested before, during, and after two types of standard care procedures: (1) nonnociceptive (eg, cuff inflation to measure blood pressure, soft touch) and (2) nociceptive (eg, tube or drain removal, endotracheal or tracheal suctioning). Receiver operating characteristic curve analysis of the NOL will be performed for Groups A and B using pain standard measures as reference criteria. Mixed linear models for repeated measures will be used to compare time points, procedures, and their interaction in each group (A, B, and C). Based on power analyses and considering an attrition rate of 25%, a total sample size of 146 patients (68 in Group A, 62 in Group B, and 16 in Group C) is targeted.

**Results:**

This study was funded in April 2020 but could not be launched until 2022 due to the COVID-19 pandemic. Recruitment and data collection began at the primary site in July 2022 and has been implemented at the secondary sites in 2023 and 2024 and is planned to continue until 2026.

**Conclusions:**

The primary strength of this study protocol is that it is based on rigorous validation strategies with the use of pain standard criteria (ie, self-report and behavioral measures). If found to be valid, the NOL could be used as an alternative physiologic measure of pain in critically ill adults for whom no other pain assessment methods are available.

**Trial Registration:**

ClinicalTrials.gov NCT05339737; https://clinicaltrials.gov/study/NCT05339737

**International Registered Report Identifier (IRRID):**

DERR1-10.2196/60672

## Introduction

### Background

Patients in the intensive care unit (ICU) are exposed to many noxious stimuli as part of standard care, which may involve nociception and pain. Although nociception and pain are interrelated, they are distinct concepts. Nociception involves the neural processes of encoding noxious stimuli that lead to autonomic (eg, increased vital signs) and behavioral responses, which may or may not imply the sensation of pain [1,2]. Pain is a personal and multidimensional phenomenon influenced by biological, psychological, and social factors [1-3]. Appropriate detection of nociception and pain is key to providing adequate analgesia during critical illness in order to reduce the risk of adverse outcomes such as prolonged mechanical ventilation, longer ICU stay, and chronic pain development [4,5].

Many ICU patients experience pain at rest, and this pain is significantly increased during nociceptive procedures as part of standard care (eg, drain or tube removal, endotracheal suctioning, line insertion, wound care, and turning) [6-9]. Behavioral responses such as grimacing and muscle rigidity are commonly observed in ICU patients during standard care procedures and have been associated with their self-reported pain [10]. While the patient’s self-report (the reference standard) is the preferred method of pain assessment, it is unsuitable for patients unable to rate their pain due to a combination of several factors affecting their capacity to communicate, such as mechanical ventilation (>33% of Canadian ICU patients) [11], sedation, or an altered level of consciousness. In such situations, behavioral assessment tools such as the Behavioral Pain Scale (BPS) [12] and the Critical-Care Pain Observation Tool (CPOT) [13] are alternative standard measures of pain in patients unable to self-report with minimal motor function to exhibit behavioral responses [14]. However, these behavioral assessment tools cannot be used in heavily sedated patients or those receiving neuromuscular blocking agents as they become unresponsive to stimulation [15].

Alternative methods for pain assessment are necessary when none of the pain standard criteria (ie, self-report or behavioral measures) can be used. Although individual vital signs (eg, heart rate, blood pressure) are easily accessible through continuous bedside monitoring, they are not valid for ICU pain assessment due to inconsistent findings across studies and clinically insignificant variation in their values (<20%) [14,16]. However, research in the field of pain and anesthesia has shown that the combination of physiologic parameters is superior to their individual values [17]. Inspired by initial data from healthy subjects exposed to tonic heat stimuli inducing different pain levels [18], the Nociception Level (NOL) index (Medasense Biometrics Ltd) is a multiparameter technology, which was further developed for nociception monitoring and related pain in anesthetized patients [19-21]. In our recent review [22] of 6 studies in anesthetized patients, the NOL index outperformed single physiologic parameters for the detection of nociception during standard care procedures and experimental stimuli [17,20,23-25].

Although the validity of the NOL is supported in anesthesia, its use in the ICU is new. To our knowledge, we are the first research team to have pilot-tested the use of the NOL for nociception and pain assessment in the ICU. We conducted 2 pilot studies in 15 mechanically ventilated [26] and 54 cardiac surgery ICU patients [27] able to self-report their pain. In both studies, discriminative validation of the NOL was supported with higher index values during nociceptive procedures (ie, chest tube removal, endotracheal suctioning) compared with rest and a nonnociceptive procedure (ie, noninvasive blood pressure [NIBP] using cuff inflation). The NOL values were positively associated with self-reported pain and CPOT scores during nociceptive procedures, providing initial evidence of criterion validation with pain standard criteria [26,27]. Also, a NOL cutoff >25 was found to adequately classify patients with moderate to severe self-reported pain intensity (>4/10) [27]. However, these pilot validation studies of the NOL were limited to 2 nociceptive procedures as part of standard care and were solely conducted in ICU patients who were able to self-report. Further validation of the NOL during various standard care procedures in critically ill adults with different levels of consciousness or sedation and in response to analgesic treatment is necessary to confirm its validity for the assessment of nociception and related pain in the ICU.

### Study Rationale, Goal, Objectives, and Research Hypotheses

An instrument can only be shown as valid for a specific purpose in a given population and context [28]. The NOL index was initially developed and validated for nociception monitoring and related pain in anesthetized patients [17,19-25]. Therefore, validating its use for nociception (primary purpose) and pain assessment (related purpose) in critically ill adults admitted to the ICU (different population and context of care) is necessary. Inspired by our pilot work, strategies for this larger validation study include: (1) criterion validation (ie, NOL’s ability to detect pain according to pain standard criteria) and (2) discriminative validation (ie, NOL’s ability to discriminate between nonnociceptive and nociceptive procedures) [28]. Considering that reliability is a necessary condition for validity [28], test-retest reliability of the NOL’s ability to generate consistent values in similar conditions (eg, at rest) will also be examined.

Research Question: Is the NOL a valid method for the assessment of nociception and pain in critically ill adults in the ICU context?

In order to answer this research question, specific validation objectives are to examine the NOL’s ability to:

Detect pain in ICU patients able or not to self-report using appropriate pain standard criteria (ie, criterion validation);Discriminate between nonnociceptive and nociceptive procedures part of standard care as well as before and after the administration of a breakthrough opioid dose (ie, discriminative validation);Generate consistent values in similar conditions (ie, pre- and post-nonnociceptive and nociceptive procedures) when ICU patients are at rest.

Our research hypotheses to be tested include:

H1. The NOL index adequately classifies ICU patients with pain based on either their self-reported pain intensity or CPOT scores.

H2. The NOL index produces higher values during nociceptive procedures compared to nonnociceptive procedures and lower values post- versus preopioid administration.

H3. The NOL index generates consistent values pre- and post-nonnociceptive and nociceptive procedures when ICU patients are at rest.

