Participants are assessed at rest before, during, and 15 minutes after nonnociceptive and nociceptive procedures that are part of ICU routine care. Whenever possible, 15 minutes postprocedure are respected to allow for the resolution of the release, reaction, and elimination of stress hormones (ie, epinephrine and norepinephrine) and stress-activated responses that may be present following noxious stimulation [33]. The nonnociceptive procedures are ideally performed prior to nociceptive procedures and include soft touch (ie, research staff touching the patient’s arm for 1 minute) and cuff inflation for blood pressure measurement (NIBP), which were empirically shown to be painless in previous studies [34], including our pilot NOL studies [26,27]. In the sequence of nonnociceptive procedures, soft touch is performed first and cuff inflation last. Then, the goal is to observe up to two nociceptive procedures per participant (Textbox 2). Nociceptive procedures are selected according to the standard care required by the patient’s condition. These procedures do not involve mobilizing the patient out of bed, as important movements may introduce artifacts in the NOL data. When possible and as required by the patient’s condition, participants are also assessed before and 15 minutes postadministration of a breakthrough dose of an opioid such as fentanyl, morphine, or hydromorphone through a parenteral route (mainly through intravenous or subcutaneous routes) to capture onset or peak of action. The decision to administer an opioid is made as per local practice and based on an assessment performed by the ICU nurse or physician. Within a window of 48 hours after obtaining informed consent, a total of 10 to 12 time points of data collection is completed with each participant during their ICU stay (Table 1).

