#### Demographic and Clinical Information for ICU Patient Participants

Demographic information (eg, age, sex, gender, and ethnicity) is collected from the patient or their representative. Information related to the patient’s clinical condition (ie, ICU admission diagnosis, mechanical ventilation, the severity of illness [Acute Physiology and Chronic Health Evaluation; APACHE II] [38], level of consciousness [GCS] [30], sedation level [RASS] [31], delirium screening with the Confusion Assessment Method-ICU [39] or Intensive Care Delirium Screening Checklist [40], according to the respective tool used at each site), as well as medication information (ie, morphine equivalent doses [41] received within 4 hours before and during the entire data collection, sedative agents, vasopressors, and use of opioids before ICU admission) is extracted from the medical records by the research staff. The following clinical information is collected at the time of obtaining consent and performing data collection: mechanical ventilation status, GCS score, RASS score, and delirium screening.

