Discriminative validation (objective 2) is our main objective to test in Group C, and paired *t* tests comparing the NOL values of each nociceptive procedure with the nonnociceptive procedure will be obtained. Generalized linear mixed model for repeated measures will allow us to compare the NOL index values across time points (pre, during, and post), procedures (nonnociceptive vs nociceptive), and their interaction in each group (A, B, and C). The generalized linear mixed model technique incorporates the full-information maximum likelihood procedure, which allows parameter estimation for missing data [47]. NOL values are expected to be significantly higher during nociceptive procedures in all 3 groups. Covariates (eg, sex, gender, morphine equivalent doses, opioid use before ICU admission) may be added if appropriate. Finally, NOL data obtained at pre- and postadministration of an opioid dose will be tested separately using paired *t* tests as not all patients will be candidates for these assessments.

For test-retest reliability (objective 3), paired *t* tests will be performed between pre and post-nonnociceptive and nociceptive procedures in all 3 groups. Nonsignificant paired *t* tests are expected to support the stability of NOL values when the patients are at rest.

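### Objective 3 counts rest before and after nociceptive procedures as test-retest pairs, although nothing in the protocol ensures or checks that the resting state stayed the same

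*Protocol article*

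**What the plan says.** The objectives (Study Rationale, Goal, Objectives, and Research Hypotheses) define the reliability question as whether the NOL can "Generate consistent values in similar conditions (ie, pre- and post-nonnociceptive and nociceptive procedures) when ICU patients are at rest". The parenthesis makes rest around nociceptive procedures part of the definition, and H3 repeats it. The same section describes reliability as a precondition of validity.

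Data Analysis carries this through: "paired *t* tests will be performed between pre and post-nonnociceptive and nociceptive procedures in all 3 groups". The success rule follows: "Nonsignificant paired *t* tests are expected to support the stability of NOL values when the patients are at rest".

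The one safeguard is in Study Procedures: "Whenever possible, 15 minutes postprocedure are respected to allow for the resolution of the release, reaction, and elimination of stress hormones", together with stress-activated responses.

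On opioids, H2 expects "lower values post- versus preopioid administration". Study Procedures leaves timing to the clinical team: "The decision to administer an opioid is made as per local practice and based on an assessment performed by the ICU nurse or physician". Table 1 gives the opioid its own pre and post columns.

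The protocol also collects data that bear on whether the state changed. Self-report on the Faces Pain Thermometer (FPT, Group A) and the CPOT score (Groups A and B) are taken at the resting time points, and the record includes "morphine equivalent doses [41] received within 4 hours before and during the entire data collection". The stated analysis of objective 3 uses none of these.

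**The concern.** A test-retest comparison can be read as reliability only if what is being measured is the same on both occasions. The pair around soft touch and cuff inflation comes close, because the protocol regards both as painless. The pairs around nociceptive procedures are different. The list includes chest tube and drain removal, which may take away a source of pain, wound care, which may leave some behind, and repositioning, which may do either.

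If resting pain moves, an index that follows pain should move with it. The planned test would then count that movement against the index. In the other direction, a nonsignificant mean difference does not show that individual readings were stable. Since the protocol makes reliability a condition for validity, an ambiguous result on objective 3 weakens what can be concluded from the study as a whole.

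**Working it through.** The protocol gives no sample size, margin, alpha or power for H3, so there is no stated figure to reproduce. The check has two parts.

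**1. Is an unchanged state ensured or verified?**
- *Interval.* The 15 minutes apply where possible. Their stated purpose is the clearing of stress hormones and stress-activated responses, not the return of pain to its earlier level. No restriction to pairs that met the interval is stated.
- *Opioid.* Dosing follows clinical need. No text keeps a dose outside a procedure's pre-post interval or removes such a pair from the H3 test.
- *Verification.* FPT and CPOT are available at rest but do not select or qualify the pairs.

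The answer is no for the nociceptive pairs.

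**2. How large a shift would matter?**

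Inputs from Sample Size Calculation: 54, 50 and 13 evaluable patients in Groups A, B and C. The only SD given is 10, for the procedure contrast. Assumptions: the SD of the rest-to-rest difference is 10 (range 5 to 15), and the test is two-sided at .05.

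The power of the paired t test comes from the noncentral t distribution with n − 1 degrees of freedom and noncentrality (shift / SD) × √n. For a shift of 4 points and SD 10 the ratio is 0.4:
- Group A: 0.4 × √54 = 2.94, power 82%
- Group B: 0.4 × √50 = 2.83, power 79%
- Group C: 0.4 × √13 = 1.44, power 26%

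Mean shift that is significant with 80% probability:

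| Group | n | SD 5 | SD 10 | SD 15 |
|---|---|---|---|---|
| A | 54 | 1.9 | 3.9 | 5.8 |
| B | 50 | 2.0 | 4.0 | 6.1 |
| C | 13 | 4.2 | 8.5 | 12.7 |

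Probability of a significant result by size of shift, SD 10:

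| Shift | n = 54 | n = 50 | n = 13 |
|---|---|---|---|
| 3 | 58% | 55% | 17% |
| 5 | 95% | 93% | 38% |
| 8 | >99% | >99% | 75% |

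*Cancelling shifts.* With +8 points in one half of the sample, −8 in the other and noise SD 10, simulation gives a significant result in about 1% of runs at n = 54 and n = 50. The reason is that the mean shift is zero while the observed SD rises to about √(10² + 8²) = 12.8. Every patient's true level has moved by 8 points, yet H3 passes.

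**The case against.** The strongest defence has four parts.

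- *H3 is compatible with the other hypotheses.* H1 is tested by ROC curves for the nociceptive procedures, H2 compares readings during procedures and around a separately scheduled opioid dose, and H3 concerns rest. A reader might infer that H3 contradicts H1 and H2. The documents do not support that. The conflict exists only for pairs in which the state changed or an opioid intervened, and no text says that either occurs. The Introduction says pain rises during procedures and is silent on rest 15 minutes later.
- *The washout is aimed at what the NOL measures.* The index is built from autonomic signals, and the interval is meant to let stress responses settle. Nociception is its primary purpose and pain the related one, so a modest change in resting pain need not move it. This is fair, but the interval is not guaranteed and its success is not checked.
- *The mechanisms pull in different directions.* Relief after one procedure and residual pain after another would partly cancel in a mean. This stands against any claim that an accurate NOL would fail H3; it only could. It also shows that passing is weak evidence of stability.
- *An index blind to pain gains nothing.* It might meet H3 easily, but it would fail H1 and H2. This stands: H3 is not the only hurdle, and the ROC analysis is primary.

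Handling of short-interval or opioid-affected pairs may also be set out in an analysis plan not shown. That would not remove the problem, because the article itself defines nociceptive pairs as equivalent conditions.

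**Conclusion.** The point holds as a flaw in how objective 3 is defined. For nociceptive pairs, a pre-post difference cannot separate measurement error from correct tracking, and the absence of a mean difference does not show that individual values were stable.

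The size is illustrative. It rests on the assumed SD of the rest-to-rest difference (10, range 5 to 15), a two-sided .05 test and a net shift in one direction. Under these, about 4 points (2 to 6) suffices for 80% probability of a significant result in Groups A and B. The same 4-point shift would usually be missed in Group C.

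The documents do not show that resting pain differs after these procedures, that opioids fall within the pairs, or that the NOL will fail H3. The comparison around the nonnociceptive procedures is not affected by the argument about procedures. This is a cheap improvement to a non-primary objective and does not affect the primary analysis.

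**What to change.** Reword objective 3, H3 and the related analysis paragraph before the data are analysed:

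1. Make the pre/post pair of the nonnociceptive block the primary evidence for reliability in all three groups. In Group C, which has no pain score, make it the only evidence.
2. Use nociceptive pairs as secondary evidence in Groups A and B. Limit them to pairs with an unchanged FPT (Group A) or CPOT (Group B) score and the 15-minute interval met, with the meaning of unchanged fixed in advance.
3. Where administration times are available, restrict all pairs, including the nonnociceptive one, to those with no opioid or sedative bolus between the readings. The article lists doses and agents but not their times, so availability has to be confirmed.
4. For the remaining pairs, report the change in resting NOL against the change in FPT or CPOT, and call it responsiveness.

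No additional measurements and no change in care are needed. The cost is fewer pairs, and so a less precise reliability estimate, most noticeably in Group C.

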## Methods

### Study Design

A prospective observational design was selected as it is appropriate for validation purposes using ICU standard care procedures in critically ill adults. The Strengthening the Reporting of Observational Studies in Epidemiology (STROBE) Statement: Guidelines for Reporting Observational Studies is used for the description and reporting of the study [29].

### Settings

This study is conducted in the ICUs of 3 tertiary-level university-affiliated health centers in Montréal, Québec, Canada. These ICUs have a total capacity ranging from 16-59 beds, and each ICU admits, on average, 1000-2750 patients annually.

### Participants

A consecutive sampling method is used to approach all eligible patients or their representatives during the study period. This sampling method aims to capture a representative sample of ICU patients able or not to self-report. Eligible ICU patients (Textbox 1) are assigned to one of the following groups:

Group A can communicate their self-report of pain and can exhibit behaviors (conscious and alert with Glasgow Coma Scale [GCS] [30] score of 13 to 15 or Richmond Agitation Sedation Scale [RASS] [31] score of 0);Group B cannot communicate their self-report but can exhibit behaviors (altered level of consciousness with GCS score of 6 to 12 with a score ≥4 on the motor subscale or RASS score of –1 to –3); andGroup C cannot communicate their self-report or exhibit behaviors (unconscious with GCS score of 3 to 5 with a score ≤3 on the motor subscale or RASS score –4 or –5 or receiving neuromuscular blocking agents).

Exclusion criteria were selected to control for potentially confounding variables that may affect the NOL signal or pain standard measures. Patients assigned to Group A who screen positive for delirium are excluded as this condition is likely to affect the reliability of their self-report of pain [32]. Patients with conditions that may seriously influence perfusion of the hands, heart rate, heart rate variability, blood pressure, repetitive or high movements due to agitation or behavioral responses (eg, agitation, cognitive, or psychiatric conditions) are also excluded, thereby strengthening the internal validity of the study. Finally, patients with *Clostridium difficile* must be excluded because the required disinfection product (ie, sodium hypochlorite 5000-6000 ppm) could damage the NOL device, according to the manufacturer.

Eligibility criteria of intensive care unit (ICU) patients.

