The NOL index is continuously monitored during the data collection time period, and values are extracted in a standardized manner as done in previous clinical studies for NOL data analysis purposes [24-27]. CPOT assessments (one-minute observation or duration of the procedure) are performed on participants from Groups A and B by research staff, and then conscious patients able to self-report (Group A) are asked to provide their self-report of pain intensity at each time point. Video recording is stopped before participants provide their self-report to avoid possible bias by the research staff, who will view the videos for CPOT scoring at a later time. Finally, demographic and clinical information is extracted from the participants’ medical files. At the end of data collection, the study equipment (ie, video camera, tripod, NOL device, and keyboard) is disinfected according to the prevention control infection procedures of each institution before being used for another patient.

List of nociceptive and nonnociceptive standard care procedures in the intensive care unit.

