**Nonnociceptive procedures**
Soft touch of the patient’s armNoninvasive blood pressure cuff inflation (NIBP)

**Table 1 table1:** Assessment time points and pain variables to be measured in each group (A, B, and C).

Measure	Nonnociceptive procedures					Nociceptive procedure 1				Nociceptive procedure 2				Analgesic^a^	
	Pre	Soft touch	Cuff inflation	Post	Pre		During	Post	Pre		During	Post	Pre		Post
NOL^b^	A^c^, B^d^, C^e^	A, B, C	A, B, C	A, B, C	A, B, C		A, B, C	A, B, C	A, B, C		A, B, C	A, B, C	A, B, C		A, B, C
Behaviors	A, B	A, B	A, B	A, B, C	A, B		A, B	A, B	A, B		A, B	A, B	A, B		A, B
Pain level	A	A	A	A	A		A	A	A		A	A	A		A

^a^Administration of an analgesic as required by the patient’s condition.

^b^NOL: Nociception Level Index.

^c^Group A: Patients are able to communicate their self-report of pain and can exhibit behaviors.

^d^Group B: Patients are unable to communicate their self-report of pain but can exhibit behaviors.

^e^Group C: Patients who cannot communicate their self-report of pain or exhibit behaviors.

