#### Alternative Reference Standard Measure of Pain–Groups A and B

The Critical-Care Pain Observation Tool (CPOT) [13] was selected for behavioral pain assessment in critically ill adults. The CPOT was used in our NOL pilot studies [26,27], and it is 1 of the 2 behavioral scales suggested as alternative reference standard measures of pain by the Society of Critical Care Medicine [14] and has been implemented in clinical practice in the 3 study ICUs. The CPOT includes 4 behavioral items: (1) facial expressions, (2) body movements, (3) muscle tension, and (4) compliance with the ventilator (for mechanically ventilated patients) or vocalization (for nonintubated patients). Each item is scored from 0-2, and the total score can range from 0-8. The CPOT has been validated in 47 studies with more than 3900 ICU patients with surgical, trauma, and medical diagnoses from various countries [34]. Consistent findings of good interrater reliability (interclass correlation coefficient [ICC] >0.60 between research staff and ICU nurses) and ability to discriminate between various nociceptive and nonnociceptive procedures were found across studies. Criterion validation of the CPOT was also supported by positive correlations (*r*>0.40) with ICU patients’ self-reported pain intensity [34]. A CPOT score >2 was found to adequately identify patients with self-reported pain (AUC>0.80) [34,36].

The research staff of all sites have been trained to use the CPOT using a standardized training session previously described [37]. Briefly, this 60-minute training session covers the description of the CPOT content and its scoring process. Patient videos are viewed to practice scoring with the tool with the goal of reaching consistent CPOT scores between raters within a total score difference of no more than 1 point.

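### Behaviour is never scored in Group C during a procedure, so a rise in NOL there cannot be attributed to patients whom the CPOT could not have assessed

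*Protocol article*

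**What the plan says.** **Who is in Group C.** Under Participants, Group C is the group that "cannot communicate their self-report or exhibit behaviors (unconscious with GCS score of 3 to 5 with a score ≤3 on the motor subscale". Two further routes are given as alternatives to this GCS rule: "or RASS score –4 or –5 or receiving neuromuscular blocking agents". The neighbouring Group B is defined by "altered level of consciousness with GCS score of 6 to 12 with a score ≥4 on the motor subscale or RASS score of –1 to" (its RASS range closes at –3).

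**Who is scored for behaviour.** Study Procedures states: "CPOT assessments (one-minute observation or duration of the procedure) are performed on participants from Groups A and B by research staff". The heading for the CPOT under Variables and Measurement Tools reads "Alternative Reference Standard Measure of Pain–Groups A and B".

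**Table 1.** The Behaviors row begins "Behaviors A, B A, B A, B A, B, C". The fourth entry is rest after the nonnociceptive procedures. Every later cell in the row, including both During cells of the nociceptive procedures, lists A and B only. Footnote e describes Group C as "Patients who cannot communicate their self-report of pain or exhibit behaviors".

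**What Group C is for.** Data Analysis makes discriminative validation the main objective in Group C, by paired t tests of NOL in each nociceptive procedure against the nonnociceptive procedure. The Conclusions of the abstract and the closing Conclusion offer the NOL as an alternative measure for patients who cannot be assessed in any other way.

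**The concern.** Group C carries the claim that matters most: that the NOL works where neither self-report nor behaviour is available. That claim needs patients who show no behaviour when the painful stimulus is applied. For the GCS and RASS routes the plan infers this from a score and never observes it under the stimulus. Both routes admit more than the lowest category: motor scores up to 3, and RASS –4 as well as –5.

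If some of these patients grimace or move during suctioning or turning, they are patients the CPOT could have assessed. They may also be the ones with the larger NOL rise. The Background reports that NOL was positively associated with CPOT scores during nociceptive procedures in the pilot studies. The probe contains an accelerometer, and Study Procedures warns that large movements may introduce artifacts. A mean rise in Group C would then mix two kinds of patient, and the data could not separate them. No analysis plan can recover behaviour that was not rated.

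**Working it through.** **1. The passages side by side**

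| Source | Group C and behaviour |
|---|---|
| Participants | Cannot exhibit behaviours; assigned by GCS 3–5 with motor ≤3, or RASS –4/–5, or neuromuscular blockade |
| Study Procedures | CPOT in A and B only |
| CPOT measure heading | A and B only |
| Table 1, During cells | A and B only |
| Table 1, Post of nonnociceptive procedures | A, B and C |
| Table 1, footnote e | Cannot exhibit behaviours |

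The single entry for C contradicts the other rows. It falls at rest, has no Pre or During partner, and no analysis described in Data Analysis uses it. Whether or not it stands, nothing is recorded about Group C behaviour while a stimulus is given.

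**2. Which routes are affected.** Under neuromuscular blockade, absence of behaviour does not rest on a score, so the point does not arise. On the GCS route a motor score above the minimum is allowed. The RASS route sets no motor limit. Because the scales are joined by "or", a patient with RASS –4 and GCS 6 with motor 4 meets both the Group B and the Group C definition.

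**3. The plan's own figure.** Sample Size Calculation gives 13 patients for a mean increase of 10, SD 10, power 80% and α .01. Taking the SD as that of the paired difference, d = 10/10 = 1.
- Noncentral t, one-sided α .01: n = 13, power 80.6%. The figure is reproduced.
- Normal approximation, two-sided: (z for α + z for power)² = 11.68, so 12, close to the stated figure.
- Noncentral t, two-sided: n = 16, with power 70.1% at 13.

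The article does not state sidedness. The point here does not dispute the 13.

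**4. How far a mixed group could move the mean (assumed values).** Sixteen recruits less 25% leave 16 × 0.75 = 12. Suppose k of the 12 show behaviour and rise by r units, and the rest do not respond. Mean rise = k·r/12.
- k = 3: 3 × 20/12 = 5.0; 3 × 25/12 = 6.25, that is 50 to 62% of the planned 10.
- k = 4: 4 × 20/12 = 6.7; 4 × 25/12 = 8.3.

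Neither k nor r comes from the documents.

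**5. How often the planned test would then be significant.** Simulated paired t test, α .01, SD 10 for each paired difference around its own mean. Ranges run from two-sided to one-sided.

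| Pairs | Patients with behaviour | Rise | Significant |
|---|---|---|---|
| 12 | 3 | 20 or 25 | about 3–6% |
| 12 | 4 | 20 or 25 | about 6–14% |
| 13 | 6 | 20 | 21–35% |
| 13 | 8 | 20 | 55–71% |

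A few such patients shift the estimated mean visibly but seldom produce a significant result. It takes about 8 of 13 for a better than even chance.

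**The case against.** The authors have reasons for not using the CPOT in Group C. The Background states, with a citation, that behavioural tools cannot be used in heavily sedated or paralysed patients because they do not respond to stimulation. The GCS rule uses the motor subscale, so it is not unrelated to behaviour. Staff confirm group assignment before data collection, and GCS and RASS are recorded both at consent and at data collection. The lone C in Table 1 is most likely a slip: the same cell in the NOL row reads A, B, C, and the text elsewhere speaks against it. Removing it alone would be clerical.

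Much of this stands. What remains is that the cited ground covers heavy sedation and paralysis, not the GCS route as such, and that the study does not test it in its own patients. The documents do not establish whether patients at RASS –4 or motor 3 show scorable behaviour, in either direction.

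A reader might infer that a positive Group C test could easily be produced by a few misclassified patients. The simulation does not support that for 3 or 4 of 12, and the documents give no ground for a larger share. The link between behaviour and a larger NOL rise is also an inference: the pilot association came from patients able to self-report, and the listed NOL parameters include no movement measure. A reader might also want the Group C conclusion to rest only on procedures without behaviour. That would select on a response measured during the stimulus and shrink an already small group, so it is not a sound replacement for the main analysis.

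**Conclusion.** The point holds for patients who enter Group C by GCS or RASS. As the plan stands, a rise in NOL in Group C would show that the index separates nociceptive from nonnociceptive procedures in patients with low consciousness scores. It would not show this for patients whom the CPOT could not assess, because nothing collected identifies them.

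The consequence is for interpretation and for the size of the effect. The validity of the paired t test and the sample size of 13 are unaffected. The size of the problem cannot be fixed from the documents, since the share of Group C showing behaviour is unknown. The mean shifts of 5.0 to 8.3 units rest on assumed shares (3 or 4 of 12), assumed rises (20 to 25) and no response in the rest. The change is worth making because recruitment is planned until 2026 and the missing information is cheap to collect.

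**What to change.** 1. Score the CPOT in Group C patients who are not under neuromuscular blockade, before and during each procedure. This can be done at the bedside or from the video. The camera set-up in Study Procedures is not restricted by group, so patients already enrolled could be rated where a recording exists. Bedside rating covers those for whom video is declined.
2. Keep the paired t test in all of Group C as the main analysis.
3. Add a sensitivity analysis limited to procedures with CPOT=0, and report procedures with any behaviour separately.
4. Reconcile the Behaviors row of Table 1, Study Procedures and the CPOT measure heading with this change. If Group C scoring is not adopted, at least resolve the single A, B, C cell against the text, and word the conclusion for patients with low consciousness scores and not for patients shown to have no behaviour.

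Cost: a brief extra rating in up to 16 patients, and edits to Table 1 and a few sentences. The CPOT=0 subset will be smaller and its estimate less precise, which is why it should support the main analysis and not replace it.
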